### Recruitment, Allocation, Concealment, and Blinding

The recruitment will occur at the study setting (Sant' Anna Institute) to reach the target sample size. Patients will be randomly allocated to in a 1:1 allocation ratio to ARAMIS or conventional neurorehabilitation group. Different researchers/operators will independently recruit patients, generate the allocation sequence, and assign participants to interventions and no member of the trial will have access to the codes up to the end. Both males and females will be enrolled due to differences in baseline pain perception (44) and to sex-treatment interactions (45). Therefore, no blocking will occur but minimization will be performed for sex-difference in pain perception, handled to ensure that any individual who might introduce bias is not involved (46). The codes of allocation will be generated using Random Number selection Microsoft Office Excel 2010 (Microsoft, Milan, Italy). Blinding of data managers and biostatisticians after assignment to interventions and also about the nature of the interventions will be ensured (47). Accordingly, who will be in charge of preparing the randomization list will be someone other than the data managers and biostatisticians (47). The allocation will never be revealed up to the end of the trial. Double data entry will be performed by two independent operators for security and data quality. To guarantee the protection of confidentiality, only the responsible secretariat of the clinical center will collect and maintain the personal information of patients. Not having a trial sponsor, auditing will be independent.

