## Introduction

### Background and Rationale

Stroke represents one of the most serious causes of death and disability-adjusted life-years lost (1) destined to keep increasing due to global aging. One of the most common long-term disabilities occurring in over 69% of cerebrovascular lesions consists of impaired motor function of the upper extremities up to hemiplegia in the following 5 years in 56% of cases (2, 3). Stroke is complicated by the occurrence of poststroke pain usually within 6 months from the acute event (4), with poststroke pain syndromes reported in up to 30%−40% of stroke outliving patients (5), chronic in 11–55% of patients (6). The latter include pain caused by different pathophysiology in which nociceptive and neuropathic features can coexist ranging from pain secondary to spasticity, shoulder pain, complex regional pain syndrome (CRPS), and headache, in 1 out of 10 stroke sufferers, that is, migraine-like in 31.3% cases (7), to central poststroke pain (8). Shoulder pain is the most frequent affecting some 30–40% of stroke survivors (6). Lenticulocapsular strokes can cause hemiparesis with consequent shoulder pain (9). The development of poststroke pain correlates to the severity of stroke and paresis is associated with a 3.1-fold higher risk for stroke-related pain (10). Unfortunately, often patients suffering from pain after stroke do not find relief in current analgesic treatment because it is not supported by clinical trials, as a consequence, guidelines are lacking (9). In fact, the systematic review and meta-analysis of literature has highlighted that very few clinical trials assess the efficacy of opioids, the most potent analgesics on poststroke pain, the number of patients is very small and these studies have not been designed specifically for this condition, thus usually not evaluating the correlation between rehabilitation, pain, and physical functioning after stroke (11). Actually, stroke survivors do not even benefit from clinical trials on the novel preventative treatment of migraine, e.g., the anticalcitonin gene-related peptide monoclonal antibody eptinezumab that can provide rapid and longer-lasting action (12). This is often due to the lack of use of pain scales for an objective pain assessment validated in specific populations, e.g., patients affected by stroke, and this problem becomes even more worrying for patients with aphasia and noncommunicative and in the pandemic emergency (13–16). Robot-assisted neurorehabilitation for patients with stroke having the Integrated Robotic System for Stroke (IRSS) prototype Automatic Recovery Arm Motility Integrated System (ARAMIS) has provided a significant improvement of motor recovery (17). It consists of two computer-controlled, symmetric, and interacting exoskeletons that impress to the paretic arm the same strength and movement of the healthy arm and it has been validated in stroke survivors. The rationale for the use of ARAMIS in poststroke neurorehabilitation of the paretic upper limb relies on the possible prevention of aberrant early plasticity. According to our working hypothesis, ARAMIS might improve plasticity in agreement with the concept underlying the Reinforcement-Induced Movement Therapy (18), avoiding the occurrence of spasticity and hypotonia.

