### Eligibility Criteria

Consecutive patients, admitted to Sant' Anna Institute with the diagnosis of stroke after hospital discharge will be enrolled, accordingly with the following inclusion criteria:

- First-ever stroke within 24–72 h from diagnosis confirmed through functional MRI scan, regardless of the side, location, and extension of the lesion;-Stroke-related hemiplegic patients of any age at hospital discharge within 48–72 h after stroke with fMRI scan of the area affected;-Severe upper limb impairment, according to the Upper Extremity Subscale of the Fugl–Meyer Motor Assessment [FMA-UE (0-35) (21)];-Absence of hemiplegic upper limb-related baseline pain based on the visual analog scale (VAS), the bedside active examination with a numerical rating and, also, the douleur neuropathique en 4 questions (DN4) for the evaluation of neuropathic prestroke pain.

Exclusion criteria will be:

-Bilateral impairment;-Presence of aphasia;-Presence of cognitive impairment, as assessed using the cognitive assessment scale for patients with stroke (22), to avoid interference of aphasia or hemispatial neglect that may occur with the commonly used Mini-Mental State Examination (23) and Montreal Cognitive Assessment (24);-Stroke diagnosis without the occurrence of hemiparesis of the upper limb;-Previous rehabilitation.

Due to the lack of specific observational tools for poststroke pain in noncommunicative patients, this pilot study will not include patients affected by aphasia and cognitive impairment. The informed consent will be obtained by healthcare operators and patients will be informed about the study and they will be provided with a consent form. No additional consent provisions for biological specimens will be needed since the latter will not be collected.

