## Discussion

Cerebrovascular accidents are often accompanied by motor disability and chronic pain. Poststroke pain consists of complex syndromes including both nociceptive musculoskeletal and neuropathic features (49). Due to its characteristics, poststroke pain is often underdiagnosed and unrelieved (50). The best management option for chronic pain consists of its prevention. To this aim, this is the first clinical trial to study the use of an IRSS in subacute neurorehabilitation after stroke. In particular, ARAMIS has provided more efficacy than conventional poststroke neurorehabilitation when applied for 7–8 weeks in the improvement of motor function and activities of daily living (17, 25, 51, 52). When the lesion is high after lateral medullary infarction, known as Wallenberg's syndrome, or in the ventroposterior part of the thalamus, central poststroke pain ensues (6). In the event hemiparesis occurs, the healthy arm may offset the effect of spasticity and locomotion (52, 53). Within this frame, ARAMIS may prevent central pain, and, concurrently, may drive correct re-organization in hemiplegic patients capturing the motions and the strength of the unaffected upper limb. In fact, ARAMIS consists of two exoskeletons with 6 degrees of freedom driven by two engines and controlling the shoulder joints to compensate for the inadequate motility and strength of the paretic arm (51). Robot-assisted motor rehabilitation and myoelectrical stimulation are demonstrated to provide reduction of the upper limb impairment (38, 39, 54–56) and pain improvement (40, 57, 58). Also, actigraphic measure systems can predict acute phase stroke prognosis (59), supporting the role of technological progress in stroke. Furthermore, the use of these devices can help the familiarization of poststroke survivors with the latter technology (60). However, a decrease in upper limb impairment does not always correlate to practical and daily functional improvement and this translational aspect needs to be studied for effective neurorehabilitation (61). In fact, the wide multicenter trial for the evaluation of robot-assisted training for the upper limb after stroke (RATULS) has demonstrated that robotic neurorehabilitation does not significantly improve the upper limb function (62). Pain intensity has been positively correlated with time since stroke and negatively with motor function (44), supporting the need to examine the role of robot-assisted rehabilitation in pain processing and to clear the mechanisms necessary for effective functional gain. The latter is a top ten priority for stroke survivors (63). Therefore, the role of ARAMIS-assisted neurorehabilitation in the prevention of poststroke pain occurring 3–6 months after stroke deserves investigation. The efficacy of robot-assisted neurorehabilitation in the prevention of chronic poststroke pain could pose the basis for a remarkable improvement of stroke sufferers' quality of life. Moreover, a better and deeper understanding of robot-related motor learning is needed (55) and, although the stage is a predictor for better rehabilitation outcomes, IRSS neurorehabilitation, without significant differences among the several devices existing (64), has proven promising results also in chronic stroke survivors (65). In this already fragile population, robot-assisted rehabilitation may also reduce the use of analgesics known to be endowed with serious side effects. In fact, fragile populations are often subjected to limited and inappropriate pain treatment (66–68). The next step will consist in investigating the effect of this neurorehabilitation procedure on the use of analgesics, both synthetic and of natural origin, as the essential oil of bergamot endowed with analgesic (69) and flumazenil insensitive anxiolytic-like (70) properties and which has been engineered allowing double-blind clinical trials (71, 72).

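### Allocation is minimised on sex alone, although the protocol itself links severity and motor function to pain and baseline FMA-UE is known at entry; the stated group comparison does not adjust for it either

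*Protocol article*

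**What the plan says.** **Allocation.** Under Recruitment, Allocation, Concealment, and Blinding, the ratio is 1:1 and "no blocking will occur but minimization will be performed for sex-difference in pain perception". Sex is the only factor named. The section justifies it by sex differences in pain perception and by sex–treatment interaction. It also says: "The codes of allocation will be generated using Random Number selection Microsoft Office Excel 2010".

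**Who enters.** Eligibility Criteria admit patients of any age with FMA-UE 0–35, a band labelled severe, and lesions "regardless of the side, location, and extension of the lesion". Stroke without upper-limb hemiparesis is excluded, and pain related to the hemiplegic limb must be absent at baseline.

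**What the protocol reports about pain.** Background and Rationale: "The development of poststroke pain correlates to the severity of stroke and paresis is associated with a 3.1-fold higher risk for stroke-related pain". The Discussion adds that pain intensity is negatively correlated with motor function, citing the same reference (44) that the allocation section cites for sex differences in pain perception.

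**Analysis.** Statistical Analysis compares the arms at t3 and t4 versus t0 by independent t-test or Mann–Whitney U test. A linear mixed model covers change over time. No covariate is named for either. A correlation between VAS pain and FMA-UE is planned at every visit. Under Outcomes, FMA-UE is also a secondary measure.

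**The concern.** The reason given for balancing sex is its relation to pain. By the protocol's own account, severity and motor function are also related to pain, and the authors expect to see that relation in their data, since they plan to correlate VAS with FMA-UE. The score has to be taken before entry, so it could be used at allocation without a new measurement. It is not used, and the group comparison described does not correct for it afterwards.

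In a single-centre trial of 118, the arms could by chance differ in baseline severity. A reader would then be unsure how much of a pain difference came from ARAMIS and how much from the starting position. The same doubt would apply to the motor outcomes, where FMA-UE is itself measured.

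**Working it through.** **Inputs from the protocol article:** 59 per arm recruited and 53 per arm before the dropout allowance; difference in means 6.34 − 5.4 = 0.94; Z values 1.96 and 0.84 (Sample Size).

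**Assumptions, not in the documents:** correlation r between baseline FMA-UE and later pain of 0.3 to 0.5; for the simulation, FMA-UE uniform over 0–35, sex split evenly, and minimisation with a biased coin of 0.8.

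**1. The plan's own figure.** The dropout step reproduces: 53/(1 − 0.10) = 58.9, so 59 per arm and 118 in all. The 53 itself cannot be reproduced, because no value is given for σ. Solving the printed formula backwards gives the standardised effect: √[2 × (1.96 + 0.84)² / 53] = √(15.68/53) = 0.544. The implied SD is 0.94/0.544 = 1.73. The 0.544 is used below only as a yardstick.

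**2. Chance imbalance when FMA-UE is left out of the allocation.** The SD of the standardised difference in means is √(2/n).

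| n per arm | SD of difference | P(more than 0.2 SD) | P(more than 0.3 SD) | 95% limits |
|---|---|---|---|---|
| 59 | 0.184 | 0.277 | 0.103 | ±0.36 SD |
| 53 | 0.194 | 0.303 | 0.123 | ±0.38 SD |

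With a median split of FMA-UE and 59 per arm (two independent binomials with probability 0.5), the arms differ by 6 or more patients (6/59, about 10 percentage points) with probability 0.311, and by 9 or more (9/59, about 15 points) with probability 0.117.

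**3. Effect on an unadjusted comparison.** Shift in mean pain = r × imbalance.

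- Imbalance 0.2 SD: 0.2 × 0.3 = 0.06 SD and 0.2 × 0.5 = 0.10 SD. Relative to 0.544, that is 11% and 18% of the implied effect.
- Imbalance at the 95% limit with 53 per arm (0.381 SD): 0.11 and 0.19 SD, or 21% and 35% of the implied effect. Given an imbalance that large, the type I error is about 8% and 13%.
- Averaged over all allocations, the simulated type I error with minimisation on sex alone was 4.6% (r = 0.3) and 5.2% (r = 0.5), so it stays near 5%.

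**4. What balancing changes** (3,000 simulated trials per setting, 106 patients). Adding FMA-UE split at its midpoint cuts the SD of the imbalance from about 0.19 to about 0.10. The chance of exceeding 0.3 SD falls from about 12% to about 0.5%. Power of the unadjusted test barely moves (about 80% to 80–82%). If FMA-UE is balanced but not adjusted for, the unadjusted test becomes conservative: simulated type I error was 3.9% (r = 0.3) and 3.2% (r = 0.5).

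**5. What adjustment changes.** The residual SD shrinks by √(1 − r²), so power = Φ[0.544/√(1 − r²) × √(53/2) − 1.96].

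- No adjustment: Φ(2.80 − 1.96) = 0.80.
- r = 0.3: 0.544/0.954 = 0.570, giving Φ(2.94 − 1.96) = 0.84.
- r = 0.5: 0.544/0.866 = 0.628, giving Φ(3.23 − 1.96) = 0.90.

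Simulated adjusted power agreed: about 83% for r = 0.3 and 88–90% for r = 0.5. Most of the gain in power therefore comes from adjustment; balancing mainly makes a conspicuous imbalance unlikely.

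**The case against.** **A reader might infer that the main known risk factor for pain is left to chance.** The documents do not say that. The only quantified risk, 3.1-fold, belongs to having paresis, and eligibility requires that of every patient, so it is constant across arms. What is left to chance is the degree of severity within a band already labelled severe. The protocol reports correlations, not causes. Nor does it say that FMA-UE within this band predicts the later onset of pain in patients who start without it. Range restriction could bring r below 0.3, and the gain would shrink with it.

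**A reader might infer that the trial would be biased.** It would not. Random allocation keeps the overall type I error near 5%, and the p-value already allows for chance imbalance. A 0.2 SD imbalance gives a shift of 11–18% of the implied effect, too little to pass for prevention by itself.

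**The analysis may already help.** Comparison against t0 lets the motor and spasticity outcomes use their own baselines, and covariates for the mixed model may stand in an analysis plan that is not shown. Their absence from the article is no fault. But baseline limb pain is absent by design, so the t0 value carries almost no information for the primary outcome, and the t-test or Mann–Whitney comparison that is stated takes no covariate.

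**Choosing FMA-UE is a judgement.** Age and lesion site are unbalanced too, and the Discussion ties central poststroke pain to lesion site. The trial is described as a pilot and exploratory, and sex is a reasoned choice. This stands: nothing in the allocation section is wrong as written on this point. FMA-UE is preferred because it is already required for entry, is linked to pain by the protocol itself, and is also an outcome.

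**Conclusion.** The point holds as an inexpensive improvement to a design choice, not as an error that threatens validity. Sex is the only balancing factor. A correlate of pain that the protocol itself names, and that is measured before entry, is neither balanced nor adjusted for in the stated comparison.

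The size is moderate: a 28% chance of an imbalance above 0.2 SD and about 10% above 0.3 SD with 59 per arm. These two figures depend only on the sample size. The consequences for pain (0.06–0.10 SD for a 0.2 SD imbalance) and for power (about 80% to about 84–90%) depend on the assumed r of 0.3–0.5. The power figures also depend on an effect of about 0.54 SD, back-solved from 53 per arm because the protocol gives no SD. What is lost is precision and the credibility of a single result.

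**What to change.** 1. In the allocation section, add screening FMA-UE as a second minimisation factor beside sex, in two prespecified bands within 0–35. A split at the midpoint (0–17 and 18–35) is one option; the documents give no basis for a particular cut. State that FMA-UE is scored and entered before the allocation is requested.
2. In Statistical Analysis, include baseline FMA-UE (as a continuous score) and sex as covariates in the between-arm analysis of the primary outcome. If pain scores prove too skewed for a linear model, a regression for ordered outcomes with the same covariates can take the place of the Mann–Whitney test. The power figures above apply to the linear model.
3. Say how minimisation, which needs the factor values of patients already allocated, works together with the Excel random-number codes. This is a separate matter but has to be settled before a factor is added.

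**Cost.** One sentence and one extra field at allocation, and slightly more work in the analysis. The score is already collected and the sample size is unchanged. The downside is that FMA-UE must be complete before allocation. The allocation change cannot be made retrospectively for patients already allocated; the covariate adjustment should be fixed before allocation is revealed.

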### Statistical Analysis

The statistical analysis plan follows the Consolidated Standards of Reporting Trials (CONSORT) evidence-based reporting guideline to ensure research transparency, specifically to trials of nonpharmacologic treatments (NPTs), as rehabilitation (48). The primary (pain) and secondary (spasticity and rehabilitation parameters) outcome measures, collected at prespecified time point *t*_3_ and *t*_4_ vs. *t*_0_, will be expressed as mean and standard error and assessed for statistically significant differences using independent *t*-test for data normally distributed or Mann–Whitney U test for skewed data. Based on the CONSORT NPT item 12b, the evaluation of the outcome measures over time will be carried out through a linear mixed model. The correlation between pain (VAS measure) and recovery (FMA-UE), assessed at *t*_0_, *t*_1_, *t*_2_, *t*_3_, and *t*_4_, will be performed through the Pearson product-moment correlation coefficient (*r*). In agreement with the CONSORT NPT item 12a, the clustering of data will be performed by blinded care providers of the center. Statistical analysis will be performed using SPSS statistics software (Chicago, IL, USA). Values of *p* < 0.05 will be considered statistically significant.

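### Allocation is minimised on sex, but the two-sample tests fixed for pain at 3 and 6 months ignore sex: a small conservative mismatch, cheap to remove

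*Protocol article*

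**What the plan says.** In the protocol article, Recruitment, Allocation, Concealment, and Blinding describes a "1:1 allocation ratio to ARAMIS or conventional neurorehabilitation group" and adds that "no blocking will occur but minimization will be performed for sex-difference in pain perception". The same section explains the attention to sex: "Both males and females will be enrolled due to differences in baseline pain perception (44) and to sex-treatment interactions (45". It also states that "The codes of allocation will be generated using Random Number selection Microsoft Office Excel 2010", and it refers to a list prepared by someone other than the data managers and statisticians.

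Statistical Analysis says that pain and the secondary outcomes, "collected at prespecified time point *t*_3_ and *t*_4_ vs. *t*_0", are compared "using independent *t*-test for data normally distributed or Mann–Whitney U test for skewed data". It adds that "the evaluation of the outcome measures over time will be carried out through a linear mixed model". Sex is not mentioned anywhere in that section, and no covariate is named for the mixed model. The section does not say whether the two-sample tests or the mixed model carry the primary conclusion.

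Eligibility Criteria requires that patients have no pain in the hemiplegic upper limb at entry.

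**The concern.** Minimising on a factor makes the arms alike on that factor. If the factor also predicts the outcome, the difference between arms varies less from trial to trial than it would under simple randomisation. A t-test that leaves the factor out does not see this. Its standard error still contains the variation between men and women, although the allocation has removed that variation from the comparison. The standard error is then larger than the true one, the type I error falls below 5%, and any interval built on it is wider than it need be.

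The protocol's own premise is that sex matters enough for pain to steer allocation. On that premise, sex belongs in the between-arm comparison. What is at stake is precision, not validity in the harmful direction.

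Taking the change from baseline does not solve this. Because entry requires no limb pain, baseline scores should be near zero in both sexes, and subtracting them leaves a later sex difference in place.

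**Working it through.** **Inputs from the protocol article (Sample Size).** Z for two-sided 5% is 1.96 and Z for 80% power is 0.84, so the planned effect is 1.96 + 0.84 = 2.80 standard errors. The means are 6.34 and 5.4, a difference of 0.94, with 53 per arm before drop-out and 59 after.

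**The plan's own figures.** 53/(1 − 0.10) = 58.9, so 59 per arm and 118 in total, as stated. The 53 cannot be reproduced directly because no value is given for the standard deviation. Working backwards, σ = √(53 × 0.94² / (2 × 2.80²)) = 1.73, a standardised effect of 0.94/1.73 = 0.544. The formulas below need only the 2.80, so they do not depend on this back-calculation.

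**Assumption.** Sex explains a share R² of pain variance within an arm, with R² = 2%, 5% or 10%. With equal numbers of men and women (also assumed), the sex difference is 2√R², that is 0.28, 0.45 or 0.63 SD.

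**Formulas (normal approximation, sex fully balanced).** The unadjusted test uses variance 2σ²/n, but the true variance is 2σ²(1 − R²)/n. Hence:

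- type I error, unadjusted = 2[1 − Φ(1.96/√(1 − R²))]
- power, unadjusted = Φ((2.80 − 1.96)/√(1 − R²))
- power, adjusted = Φ(2.80/√(1 − R²) − 1.96)
- ratio of unadjusted to true standard error = 1/√(1 − R²)

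| R² | SE ratio | Type I error, unadjusted | Power, unadjusted | Power, adjusted | Gain (points) |
|---|---|---|---|---|---|
| 2% | 1.010 | 4.8% | 80.2% | 80.7% | 0.5 |
| 5% | 1.026 | 4.4% | 80.6% | 81.9% | 1.4 |
| 10% | 1.054 | 3.9% | 81.2% | 83.9% | 2.7 |

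Gains are taken before rounding.

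**Check by simulation.** 40,000 trials per setting, 106 patients analysed, half women, standardised effect 0 or 0.544. Minimisation on sex used a biased coin of 0.8 or was deterministic. The t-test was compared with a linear model on arm and sex.

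| Sex difference (R²) | Type I error, t-test | Type I error, adjusted | Power, t-test | Power, adjusted |
|---|---|---|---|---|
| 0.3 SD (2%) | 0.047–0.048 | about 0.050 | 79.2–79.3% | 79.9–80.0% |
| 0.5 SD (6%) | 0.041–0.045 | 0.048–0.052 | 79.6–79.7% | 81.4–81.5% |
| 0.8 SD (16%) | 0.032–0.033 | 0.049–0.052 | 81.1–81.3% | 85.5–85.8% |

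At 0.5 SD the t-test's average standard error was 0.194 against a true 0.188–0.190. At 0.8 SD it was 0.194 against 0.178. With no sex effect the two analyses agree.

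**If allocation is simple randomisation.** The t-test's simulated type I error stayed at 0.048–0.052 for every sex effect tried. Power was 78.5% unadjusted against 79.1% adjusted at 0.3 SD, and 78.8% against 81.0% at 0.5 SD.

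These figures are for the t-test. No figure was computed for the Mann–Whitney test, which omits sex in the same way.

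**The case against.** The strongest reply has four parts.

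First, the article does not rank its analyses. A reader might infer that the t-test or Mann–Whitney test decides the trial, but the text does not say so. The mixed model could carry sex, and its covariates are commonly left to an analysis plan that is not shown. This stands, and the model's silence on covariates is not in itself a fault. It does not remove the point about the two-sample tests: they are fixed by name and cannot carry sex, so a plan that adjusted for sex at 3 and 6 months would have to replace them.

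Second, it is unclear whether minimisation is really used. Excel random codes and a prepared list fit poorly with it. This also stands. The claim about the standard error is therefore conditional, and under simple randomisation only the precision loss is left.

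Third, the harm is small and in the safe direction. A reader might infer that omitting sex throws away the benefit of minimising. It does not: balance still reduces the true variability of the unadjusted difference, and only the estimated standard error fails to show it. For the same reason the unadjusted test should not be credited with a flat 80% power under forced balance. Its power rises slightly too, which shrinks the gain from adjusting.

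Fourth, a reader might infer from the mention of sex-treatment interactions that the trial owes an interaction analysis. The article cites them only as a reason to enrol both sexes. Objectives and Outcomes do not list an interaction, and a trial that calls itself a pilot and exploratory need not estimate one.

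**Conclusion.** The mismatch is real but small. It rests on two conditions: that minimisation on sex is carried out as stated, and that sex predicts pain at 3 and 6 months, as the protocol itself supposes. Under both, the unadjusted standard error is about 1% to 5% too large for an assumed R² of 2% to 10%, and adjusting gains about 0.5 to 2.7 points of power. At a sex difference of 0.3 SD or less the effect is negligible. It becomes material only for large effects, such as 0.8 SD, which lies above the assumed range.

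The documents do not support a claim of bias, of false positives, or of an invalid trial. The change is still worth making, because the balancing factor is already recorded and the adjusted analysis is sound under either method of allocation.

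**What to change.** In Statistical Analysis:

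- Replace the unadjusted t-test at 3 and 6 months with a linear model of the outcome on arm and sex.
- Include sex as a fixed effect in the linear mixed model.
- For skewed scores, replace the Mann–Whitney test with a sex-stratified rank test (van Elteren) or a re-randomisation test. This provision should be kept, because patients enter without limb pain and many follow-up scores may be at or near zero. A re-randomisation test needs the actual allocation rule to be written down.

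The cost is one degree of freedom and slightly more analysis work. No new data are needed, since sex must be recorded for minimisation, and the sample size does not change.
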